## Abstract

**Background:**

Bacterial vaginosis (BV) affects 30–50% of women at some time in their lives and is an embarrassing and distressing condition which can be associated with potentially serious comorbidities. Current antibiotic treatments such as metronidazole are effective but can result in side effects, and recurrence is common. This trial aims to investigate whether lactic acid gel is clinically effective and cost effective in the treatment of recurrent BV compared with metronidazole.

**Methods:**

VITA is an open-label, multicentre, parallel group randomised controlled trial for women with a clinical diagnosis of BV and at least one previous BV episode in the past 2 years. Participants will be randomised 1:1 to intravaginal lactic acid gel 5 ml once daily for 7 days or oral metronidazole tablets 400 mg twice daily for 7 days. All participants will be followed up for 6 months to assess health status and healthcare costs. A subgroup will be interviewed to further explore adherence, tolerability and acceptability of treatment. The estimated sample size is 1900 participants to detect a 6% absolute increase in response rate to 86% in those receiving lactic acid gel. The primary outcome is participant-reported resolution of BV at Week 2.

**Discussion:**

Results from this trial will help inform UK treatment guidelines for BV and may provide an alternative effective treatment for recurrent episodes of this condition which avoids repeated exposure to antibiotics.

**Trial registration:**

ISRCTN, ISRCTN14161293. Registered on 8 September 2017.

## Background

Bacterial vaginosis (BV) is a common condition which causes an offensive smelling vaginal discharge and is associated with an increased risk of HIV acquisition and transmission, pelvic inflammatory disease and adverse pregnancy outcomes [1–4]. The normal bacteria found in the vagina include numerous lactobacilli which produce lactic acid maintaining a low pH and inhibiting the growth of other bacteria. In BV the pH rises in association with loss of lactobacilli and there is an overgrowth of anaerobic bacteria.

Current treatment with oral antibiotics to reduce the associated overgrowth of bacteria in the vagina can be effective in the short term, but it is frequently associated with side effects and 30% rate of recurrence over the subsequent 3 months [5–8], necessitating repeated antibiotic treatment. Knowledge of the underlying pathogenesis of BV is limited and the factor(s) initiating BV are unknown, although viral bacteriophages, novel sexually transmitted bacteria, bacterial biofilms and disruption to the bacterial microbiome have all been proposed [9].

BV was diagnosed in 100,636 women attending sexual health clinics in England in 2014, and around 30,000 women will have recurrent BV within 3 months of their initial treatment. The prevalence of BV has not changed significantly over the past 5 years (https://www.gov.uk/government/statistics/sexually-transmitted-infections-stis-annual-data-tables).

The recurrent nature of BV leads to frequent use of antibiotics. The use of lactic acid gel as treatment would reduce antibiotic exposure in the population as recommended in the ‘Action plan to support the UK antimicrobial resistance strategy 2013 to 2018’ (www.gov.uk/government/publications/uk-5-year-antimicrobial-resistance-strategy-2103-to-2018) and the ‘European strategic action plan on antibiotic resistance 2011–2016’ (www.euro.who.int/_data/assets/pdf_file/0011/148988/RC61_Pres_Rodier_antibiotic_resistance.pdf).

Lactic acid gel (pH 4.5) used intravaginally replicates the production of lactic acid by lactobacilli in the normal vagina. Previous small studies of daily intravaginal acid gel or pessary for the treatment of BV have reported inconsistent results, with efficacy ranging between 18 and 100% [6, 10–15]. The regimen used most commonly in previous trials was once daily application for 1 week, and an increased frequency of dosing did not affect the response rate (efficacy 23–93% for once daily versus 18–100% for twice daily). To permit comparison with previous trials, to maximise participant acceptability and because the effectiveness of this regimen remains unconfirmed, we propose using 4.5% lactic acid gel inserted intravaginally once a day for 7 days. Although the use of topical lactic acid gel is not recommended in current BV treatment guidelines due to a lack of evidence from well-designed randomised trials [7], the proposed trial will advance our understanding by assessing whether intravaginal lactic acid gel is effective and well tolerated for the treatment of recurrent BV, and can reduce antibiotic usage in this large group of women.

The factors affecting the acceptability of topical treatment for BV are not known, and a qualitative assessment of adherence to and acceptability of treatment, and how these can be improved, will be performed.

BV is a common disease with serious physical and psychological sequelae. There is therefore the potential for substantial health gain if a more effective and well-tolerated regimen can be identified, which also reduces antibiotic exposure. The prospects for the study findings to influence clinical practice are high based on the multicentre approach including primary care, robust study design, existing availability of lactic acid gel and identified need to limit antibiotic use to reduce the development of antimicrobial resistance.

### Justification for design

This trial will compare the effectiveness, tolerability, adherence, acceptability and cost effectiveness in participants with BV randomised to intravaginal lactic acid gel (intervention) versus those randomised to oral metronidazole (control). A pragmatic trial design is used to maximise its relevance to patients and clinicians and to facilitate rapid adoption into clinical practice. A qualitative assessment will also investigate the acceptability of treatment, and if necessary, address issues raised by participants.

A superiority design has been chosen and powered to detect an absolute difference of 6% in the resolution of BV between the two treatment arms, with an assumed effectiveness of oral metronidazole of 80% [16–19].

There will be no blinding of participants to treatment, as this will maximise treatment compliance and allow comparison of the acceptability of the two treatments. A double placebo (“double dummy”) design for oral versus vaginal modes of treatment delivery was not considered to be acceptable to most women.

Participants will take their own vaginal samples at baseline and at the Week 2 follow-up. The taking of such samples is widely used in clinical practice and is acceptable to women. At their baseline visit, participants will be instructed on how to take their own vaginal samples; they will then take their own baseline samples, which will be shipped to a central laboratory by site staff. Before they leave the clinic (or General Practitioner [GP] practice), participants will be provided with a second sampling kit and instructions for taking their own vaginal samples at home at Week 2.

After the baseline visit, participants will not be required to attend any further face-to-face visits, reflecting usual clinical practice. All follow-up data will be collected by participants via online questionnaires.

### Choice of treatment

The aim of this trial is to determine if using lactic acid gel in the vagina to ‘replace’ vaginal acidity is better than oral metronidazole for treatment of BV. Some previous studies have suggested that this approach could be successful, but they are not conclusive, and current guidelines highlight a need for more evidence before recommending the use of intravaginal lactic acid gel.

Previous small studies of daily intravaginal acid gel or pessary for the treatment of BV have reported inconsistent results with efficacies of 18–100% [6, 10–15, 20]. The regimen used most commonly in previous trials was once daily application for 7 days, and an increased frequency of dosing did not affect the response rate (efficacy 23–93% for once/day compared with 18–100% for twice/day). To permit comparison with previous trials, the intervention group will receive a regimen of lactic acid gel inserted intravaginally once a day for 7 days, to maximise participant acceptability and because the effectiveness of this regimen remains unconfirmed.

If effective, the use of lactic acid gel will result in decreased antibiotic treatment use, which will maintain the balance between the gut bacteria (microbiome) for individual participants and reduce the potential for development of antimicrobial resistance in the community. In addition, it will provide an alternative treatment for women who have failed to respond to current treatment for BV with systemic antibiotics.

The control group will receive a 7-day course of twice daily 400 mg oral metronidazole. This has been chosen as the comparator because it is recommended as first line therapy in the UK national BV treatment guideline [7], it is active against a wide range of the anaerobic bacteria associated with BV and it is commonly used in clinical practice supported by evidence from randomised controlled trials [18].

## Methods/design

### Aims and objectives

The trial hypothesis is that intravaginal lactic acid gel is clinically effective and cost effective in the treatment (i.e. resolution of symptoms) of women with recurrent BV compared with oral metronidazole. The aim is to test this hypothesis by comparing symptom resolution in the intervention group (receiving intravaginal lactic acid gel) with the control group (receiving oral metronidazole) for women with recurrent BV.

The primary objective of the trial is to determine whether intravaginal lactic acid gel is better than oral metronidazole for symptomatic resolution of recurrent BV. Secondary objectives include the following: comparing the time to first recurrence of BV symptoms; comparing the frequency of BV episodes over 6 months; comparing the frequency of BV treatments required over 6 months; comparing microbiological resolution of BV on microscopy 2 weeks after presentation; comparing the tolerability profiles of lactic acid gel and metronidazole; comparing adherence to lactic acid gel versus metronidazole tablets; comparing acceptability of use of lactic acid gel versus metronidazole tablets; determining comparative presence of concurrent sexually transmitted infections (STIs) at baseline and at Week 2; comparing quality of life (measured using the SF-12™ Health Survey [21]); comparing the cost effectiveness of using intravaginal lactic acid gel versus oral metronidazole tablets. In addition, samples for further microbiological analysis, including gene sequencing, will be collected for future investigation into the factors associated with successful treatment.

### Outcome measures

The primary outcome is resolution of BV based on participant-reported resolution of symptoms at Week 2. Secondary outcome measures are as follows: time to first recurrence of BV; number of participant-reported BV episodes over 6 months; number of participant-reported BV treatment courses over 6 months; microbiological resolution of BV on microscopy of vaginal smears at Week 2; comparative tolerability of lactic acid gel and metronidazole assessed by web-based participant reporting of side effects (including nausea, vomiting, taste disturbance, vaginal irritation, diarrhoea and abdominal pain) and via participant telephone interviews; participant-reported adherence to treatment; acceptability of treatments via qualitative assessment in a subgroup of participants; prevalence of concurrent STIs (gonorrhoea, chlamydia and trichomoniasis) at baseline and at Week 2; quality of life as assessed by SF-12™ Health Survey at baseline, Week 2 and 6 months; comparative cost effectiveness of using intravaginal lactic acid gel versus oral metronidazole tablets via National Health Service (NHS) Service use questionnaire.

### Design and setting

This is an open-label, multicentre, parallel group, randomised controlled trial. Participants will be randomised 1:1 to receive either intravaginal lactic acid gel treatment or oral metronidazole tablets.

Women will be recruited from primary care (GP) practices and sexual health outpatient and gynaecology clinics in the UK (Fig. 1).

**Fig. 1 Fig1:**
[figure not shown]
VITA participant pathways in primary and secondary care settings

The Standard Protocol Items: Recommendations for Interventional Trials (SPIRIT) checklist is provided as Additional file 1.

#### Primary care (GP practices)

Primary care practices will involve the following:
Opportunistic identification of women presenting with BV in GP practices which are VITA recruiting centres with trained research staff on-site. Participants will be identified, consented, randomised and prescribed trial treatment at the practice. These research-ready sites require on-site availability of trained research nurses and facilities to directly consent and randomise patients.Opportunistic identification and referral of women with BV attending GP practices without on-site research staff, i.e. Participant Identification Centres, to refer women presenting with BV to local participating VITA recruiting centres for invitation to participate in the trial.Pre-identification of women with a history of BV by GPs from electronic patient records/primary care databases. GPs will provide potential participants with information on the trial via telephone or letter and invite them to attend a local recruiting centre for consent if they develop BV and are interested in participating.

#### Secondary care

Secondary care practices will involve the following:
Opportunistic identification of women presenting with BV in sexual health centres which are VITA recruiting centres with trained research staff on-site. Participants will be identified, consented, randomised and dispensed trial treatment at the centre. These research-ready sites require on-site availability of trained research nurses and facilities to directly consent and randomise patients.Opportunistic identification of women presenting with BV in gynaecology clinics which either (a) are VITA recruiting centres with trained research staff on-site where participants would be identified, consented, randomised and prescribed trial treatment within the clinic, or (b) act as VITA referral clinics (Participant Identification Centres) where women presenting with BV may be referred to a nearby participating recruiting sexual health centre for invitation to participate in the trial.

### Participants

The flow of participants from presentation through to follow-up is shown in Fig. 2. Inclusion criteria are as follows: age 16 years or over; clinical diagnosis of BV based on patient-reported symptoms of discharge with an unpleasant (typically fishy) odour (with or without positive microscopy according to local site practice); history of at least one previous episode of BV within the past 2 years (clinically diagnosed or patient reported) which resolved with treatment; willing to use either intravaginal lactic acid gel or oral tablets for the management of BV; willing to take own vaginal samples; willing to avoid vaginal douching during treatment; willing to provide contact details and be contacted for the purpose of collecting follow-up information; willing to avoid sexual intercourse or use effective contraception for the 7-day duration of study treatment (condoms are not considered to be effective contraception due to a potential interaction with lactic acid gel); access to the Internet and email and willing to complete web-based follow-up questionnaires in English; provision of written informed consent.

**Fig. 2 Fig2:**
[figure not shown]
Participant flow

Exclusion criteria are as follows: contraindications or allergy to lactic acid gel or metronidazole tablets; pregnant or breastfeeding; patients currently trying to conceive; use of oral antibiotics (other than the study treatment) or antifungal agents concurrently, within the last 2 weeks or planned use within the next 2 weeks; use of topical vaginal antibiotics, antifungals or acidifying products (other than the study treatment) concurrently, within the last 2 weeks, or planned use within the next 2 weeks; previous participation in this study; current participation in another trial involving an investigational medicinal product (IMP).

### Contraindications and concomitant medications

#### Metronidazole

As per exclusion criteria, any known hypersensitivity to metronidazole, other nitroimidazole derivatives or any of the ingredients in metronidazole tablets will exclude patients from the trial. The metronidazole summary of product characteristics (SmPC) gives further details, but the following should be noted:
Alcohol should be avoided (including products containing alcohol) during the course of treatment and for 48 h afterwards.Elevated international normalised ratio (INR) and bleeding events have been reported with concurrent use of warfarin and metronidazole.

#### Lactic acid gel

There is no SmPC for lactic acid gel, but the following should be noted:
Shellfish allergy: Some lactic acid gel brands may contain glycogen obtained from oysters.Condom use: The effects of lactic acid gel on condom degradation have not been fully determined. Therefore, it is advised that condoms should not be assumed to be an effective method of contraception during the 7-day treatment period with lactic acid gel.

#### Concomitant medications

Concomitant medications relevant to BV, such as oral or topical antibiotics and/or antifungals, should be recorded at baseline to determine patient eligibility. The use of additional treatments is permitted after completion of the 7-day study treatment at the discretion of the participant’s physician.

### Screening and consent

Women either pre-identified by, or presenting to, referring or recruiting GP practices, sexual health centres or gynaecology clinics with symptoms of BV will be approached by a member of the site research team to determine whether they are interested in participating in the trial. They will be given a verbal explanation of the trial along with a Participant Information Sheet, and they will have time to read this and ask any questions about the trial prior to consent. Written informed consent will be requested during the same clinic visit.

Separate optional consent will be required for any participants who are interested in taking part in the qualitative telephone interview. Participants recruited from sexual health centres and gynaecology clinics will additionally be asked for their optional consent to inform their GP that they are taking part in the trial.

### Randomisation

Randomisation will take place in primary care (GP) practices or outpatient sexual health/gynaecology clinics. Participants will be randomised 1:1 to lactic acid gel or metronidazole using a remote Internet-based randomisation system developed and maintained by the Nottingham Clinical Trials Unit (NCTU). The concealed allocation system will use a minimisation algorithm with the following variables and levels: site, type of site (GP practice, sexual health clinic, gynaecology clinic), number of episodes of BV in the previous 12 months (0, 1–3, > 3) and whether the participant has had a female sexual partner in the previous 12 months (yes/no). The allocation system will be created by the NCTU in accordance with their standard operating procedure (SOP) and held on a secure University of Nottingham server.

As this is an open-label trial, there will be no blinding of the participants, investigator, site research team or trial team to treatment allocation. However, the central laboratory staff performing BV microscopy and STI testing will be blinded to the participants’ treatment allocation, and all analyses that present data separately by treatment arm or that estimate between-group effects will be conducted by a statistician blinded to treatment allocation.

### Trial intervention

There are two treatment arms within the trial:
Lactic acid gel; 5 ml to be inserted into the vagina before bedtime once per day for 7 daysMetronidazole tablets; 400 mg to be taken orally twice daily, approximately 12 h apart, for 7 days. Tablets should be swallowed whole, taken during or after meals with a glass of water and not crushed or chewed.

#### Investigational medicinal product

Metronidazole tablets are an IMP in the trial and are licensed for use in the treatment of BV as per the SmPC.

#### Medical device

Lactic acid gel is a registered medical device consisting of a colourless viscous gel administered through an intravaginal tube applicator. Known side effects of lactic acid gel include vaginal irritation, e.g. redness, stinging and itching. In rare cases an allergic skin reaction, e.g. severe redness, swelling or burning, may occur.

### Treatment supplies, labelling and storage

Participants will receive their study treatment via the routine method of dispensing used in the setting of the recruiting centre. In sexual health centres and gynaecology clinics, this may be via issuance from standard clinic stocks. In primary (GP) care practices, allocated treatments may be issued via standard prescription as per routine care. Participants will be advised to obtain their allocated study treatment from any dispensing pharmacy. Any licensed brands of metronidazole or lactic acid gel may be used.

Trial-specific labelling will not be required, as the IMP is being used within the terms of its marketing authorisation in the UK. The IMP will be dispensed to a participant in accordance with a prescription given by an authorised healthcare professional and labelled in accordance with the requirements of Schedule 5 to the Medicines for Human Use (SI 1994/31 94) (Marketing Authorisations Etc.) Regulations 1994 that apply in relation to relevant dispensed medicinal products.

The IMP should be stored as per manufacturer’s instructions. Recruiting sexual health centres and gynaecology clinics should record batch number(s) and manufacturer(s) of all allocated treatments.

### Dosing schedule

Treatment should be started on the day of receipt, but participants will be instructed to record their actual start date and time (morning or evening) of dosing in their patient diaries. Participants will also be asked to use their patient diaries to log all subsequent doses taken and/or missed doses over the treatment period in order to aid compliance to the treatment schedule.

No treatment or dose modifications are expected in this trial. Where a dose is accidentally missed, participants will be advised to follow the manufacturer’s instructions or seek advice from their physician. In the case of any missed dose, participants will be advised to continue to complete their treatment course.

### Trial assessments and procedures

All assessments and procedures to be performed at each time point for participants are indicated in Fig. 3. Most assessments will be done at baseline, including demographics, symptoms and previous BV episodes, medical and sexual history, concomitant medications, contraception and condom use, SF12™ Health Survey and vaginal samples for BV/STI screening (sites will send the baseline samples to a central laboratory at University Hospitals Birmingham NHS Foundation Trust which is accredited under the UK Accreditation Service to perform the tests). After randomisation into the trial, participants will then take their first dose of trial treatment and continue taking trial treatment for 7 days. At Week 2, participants will take their own vaginal samples and send them to the central laboratory. They will also complete a web-based questionnaire with details of symptoms, treatment adherence and tolerability, any known side effects, healthcare use, additional BV treatments, sexual history, contraception/condom use and another SF12™ Health Survey. Participants will be asked to complete a further two web-based questionnaires at 3 months and 6 months with details of BV recurrence, sexual history, healthcare use, additional BV treatments, contraception/condom use and a final SF12™ Health Survey (6 months only). Those not responding to requests to complete web-based questionnaires will be contacted by phone and/or text to collect follow-up data.

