#### Power calculation/sample size calculation

Assuming that 80% of participants receiving oral metronidazole achieve resolution of symptoms, 1710 participants are required for analysis to detect a 6% increase in response rate to 86% in participants receiving lactic acid gel (risk ratio 1.08) at the 5% SL (two-sided) with 90% power.

To allow for non-collection of the primary outcome from up to 10%, e.g. due to loss to follow-up, a total of 1900 participants will be recruited.

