#### Health economics

The economic analysis will compare the costs associated with the current standard treatment, metronidazole, with those of the proposed alternative treatment, lactic acid gel, in the treatment of BV.

The economic evaluation will adopt the perspective of the NHS, and data on resource use and costs will be collected prospectively within the study. Resource use data will be collected prospectively via nurse/assessor/participant completed forms and will include questions on treatment use, GP or other clinic visits to estimate the costs associated with the administration of both treatments. The main resources to be monitored include: (1) additional staff time for explaining the lactic acid intervention and responding to concerns associated with treatment; (2) time and resources associated with clinical examination, additional medication and monitoring during the follow-up period as well as treating any adverse events; (3) the costs associated with treatment, for example the costs of lactic acid gel and applicators.

Information on unit costs or prices will be attached to each resource item in order that an overall cost per patient successfully treated at 2 weeks, 3 months and 6 months can be calculated, and a cost per quality-adjusted life year (QALY) at 26 weeks. The cost associated with antibiotic resistance to add as a penalty cost for using antibiotics has been estimated [22], and within this study we will explore whether a similar approach could be taken.

Outcomes will be measured in natural units according to assessment of symptoms of BV at 2 weeks, 3 months and 6 months post intervention.

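### No quality-of-life score is taken between Week 2 and 6 months, so the 26-week QALY is thinly supported; adding the SF-12 to the existing 3-month questionnaire is a cheap, partial improvement

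*Protocol article*

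**What the plan says.** Outcome measures lists "quality of life as assessed by SF-12™ Health Survey at baseline, Week 2 and 6 months". Trial assessments and procedures agrees: after Week 2, women receive "a further two web-based questionnaires at 3 months and 6 months with details of BV recurrence", and these also ask about healthcare use and additional BV treatments, but the schedule provides only "a final SF12™ Health Survey (6 months only" after Week 2.

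Health economics plans "a cost per quality-adjusted life year (QALY) at 26 weeks". The other economic outcome does use the 3-month contact: "Outcomes will be measured in natural units according to assessment of symptoms of BV at 2 weeks, 3 months and 6 months post intervention". The Background gives the expected course after oral antibiotics as a "30% rate of recurrence over the subsequent 3 months".

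The article does not say in words that the QALY is derived from the SF-12, nor how utilities are joined between assessments. The SF-12 is the only quality-of-life instrument it names, so it is presumably the source.

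**The concern.** A QALY needs utility over the whole horizon. Here a 24-week stretch is described only by a score soon after treatment and a score at 6 months, and much of the expected recurrence falls between them. A woman who relapses at 2 months, is re-treated and is well at 6 months shows no loss. The costs of her relapse are collected, but its effect on quality of life is not.

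Cost effectiveness is part of the trial hypothesis, and recurrence is a main route by which the arms could differ after Week 2. An analysis plan can choose how to interpolate, but it cannot recover a score that was never collected. The contact at which it could be collected already exists.

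**Working it through.** **The plan's own figures.** The article gives no figure for QALY precision or SF-12 coverage. Its only sample-size figure concerns the primary outcome: "Assuming that 80% of participants receiving oral metronidazole achieve resolution of symptoms" and "1710 participants are required for analysis to detect a 6% increase in response rate to 86"%. The uncorrected formula gives 822 per arm. With the continuity correction this becomes 822/4 × [1 + √(1 + 4/(822 × 0.06))]² = 855 per arm, so 1710, and 1710/0.90 = 1900. Both figures reproduce, and the present point does not depend on them.

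**Inputs from the article.** SF-12 at weeks 0, 2 and 26; a questionnaire at 3 months (taken as week 13); a QALY horizon of 26 weeks; recurrence of 30% in 3 months.

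**Assumptions, not in the article.** Area-under-the-curve (trapezoid) scoring; episodes lasting D = 2 or 4 weeks; a score that reflects the woman's state on the day; a utility decrement of 0.05–0.10 per episode; a 10-point arm difference in recurrence.

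**Step 1: weight of each score.**

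| Schedule (weeks) | Weights (weeks) | Share of QALY | Longest gap |
|---|---|---|---|
| 0, 2, 26 | 1, 13, 12 | 4%, 50%, 46% | 24 weeks |
| 0, 2, 13, 26 | 1, 6.5, 12, 6.5 | 4%, 25%, 46%, 25% | 13 weeks |

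The gap from Week 2 to week 26 is 24/26 = 92% of the horizon.

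**Step 2: share of the recurrence loss captured in the group mean.** Most episodes leave no trace, but one that is active at an SF-12 assessment is counted for that score's full weight. So:

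- weeks counted now = 12 × P(active at week 26)
- weeks counted with a 3-month score = 12 × P(active at week 13) + 6.5 × P(active at week 26)
- captured share = weeks counted / expected symptomatic weeks up to week 26

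Three onset patterns after Week 2 were tried:

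- *Uniform over weeks 2–26.* P(active) = D/24 at either visit, and true weeks = D − D²/48. For D = 2: now 1.00/1.92 = 52%, with week 13 1.54/1.92 = 80%. For D = 4: now 2.00/3.67 = 55%, with week 13 3.08/3.67 = 84%.
- *Constant hazard giving 30% in 13 weeks*, λ = −ln(0.70)/13 = 0.0274 per week. For D = 2: P(active) is 0.0417 at week 13 and 0.0292 at week 26, with 0.936 true weeks. Now 0.350/0.936 = 37%; with week 13 0.690/0.936 = 74%. For D = 4: P(active) is 0.0858 and 0.0600, with 1.812 true weeks. Now 0.720/1.812 = 40%; with week 13 1.420/1.812 = 78%.
- *All onsets uniform over weeks 2–13.* None is active at week 26, so now 0%. With week 13: 12 × (D/11)/D = 109% for either D.

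**Step 3: absolute size.** Loss per episode = decrement × weeks/52: 0.05 × 2/52 = 0.0019 and 0.10 × 4/52 = 0.0077 QALY. A 10-point difference in recurrence gives 0.0002–0.0008 QALY per woman in total. If 37–55% is captured, 45–63% is missed: 0.00019 × 0.45 to 0.00077 × 0.63, or about 0.0001–0.0005. If all recurrences are early, the whole amount is missed.

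**Step 4: sensitivity to recall.** The article does not state the SF-12 recall period. With a 4-week window and 2-week episodes, about 25% of episodes with uniform onset would touch the 6-month score. If each then showed the full decrement, 0.25 × 12 = 3.0 weeks would be counted against 1.9 true weeks. A long recall period could therefore turn the shortfall into an over-count. It would not help with early recurrences: an episode starting before week 13 and lasting 4 weeks ends by week 17, before a window covering weeks 22–26.

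**The case against.** The sections agree with each other, so there is no contradiction, and a denser schedule is a design preference on one secondary economic output. That is right, and it limits the point to an improvement. The derivation of utilities, the interpolation rule and any scenario analyses may sit in a fuller health-economics plan, so their absence from the article is not a fault.

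A reader might infer that all quality-of-life loss from recurrences is left out. The arithmetic does not support that. Women symptomatic at 6 months have a short episode weighted as 12 weeks, which in the group mean partly makes up for those whose episodes are unseen. The loss is fully missed only if recurrences are all early, and the article gives no rate beyond 3 months.

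A reader might also infer a bias towards a particular arm. The article does not show which arm will recur more, and Week 2 non-responders are themselves carried forward with a 13-week weight, so the net direction is not established.

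The size is small. If the SD of the 26-week QALY were 0.03–0.06 (an assumption), the standard error of the arm difference with 1710 women would be 2 × SD/√1710 = 0.0015–0.0029, larger than the whole amount at stake. Recurrence is also not invisible to the economics: episodes, treatments and healthcare use are recorded at 3 and 6 months, and a cost per patient successfully treated is planned at each time point.

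What survives is that the schedule is fixed in the article, the uncollected score cannot be recovered later, and the remedy needs no new contact.

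**Conclusion.** The point holds as a cheap improvement to the cost-per-QALY result only. The primary outcome, the sample size and the clinical secondary outcomes are unaffected. On the stated assumptions, capture of later recurrence loss would rise from about 37–55% to about 74–84%, or from none to about 109% if all recurrences come before week 13. The remedy is therefore real but imperfect: short episodes between visits would still be missed, and a slight over-count is possible.

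The percentages rest on four assumptions that the article neither confirms nor excludes: that the QALY comes from the SF-12, area-under-the-curve scoring, episodes of 2–4 weeks, and scores reflecting current state. The absolute figures also rest on the assumed decrement and recurrence difference. The most secure part needs only the first: 24 of 26 weeks depend on two end scores.

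**What to change.** Add the SF-12 to the existing 3-month web questionnaire, changing Outcome measures and Trial assessments and procedures to match. Recruitment opened in October 2017, so women already past 3 months would be treated as missing at that time point. The cost is a minor amendment and twelve more items, with a little extra respondent burden on a questionnaire that also carries the recurrence data.

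Alternatively, or in addition, report a scenario cost per QALY under Health economics that applies a within-trial utility decrement to recurrences reported at 3 and 6 months. Episodes current at an SF-12 assessment must be excluded, because the score already reflects them. If the decrement is taken from the change between baseline and Week 2, the report should note that recent side effects may affect it. This needs no new data, only analyst time.
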